**Local recruitment (local press**

**posters in pharmacies, doctors’ waiting**

**rooms) and at medical visits**

Assessment at D0

Intervention (spa therapy, group therapeutic education and back guide)

Follow-up at 3 months, 6 months and 1 year by post or email

+ numeric pain scale every fortnight by telephone

|  | **Enrolment visit + randomisation** | **Intervention**  **Visit** | **Visit 1**  **Mail/**  **phone** | **Visit 2**  **Mail/**  **phone** | **Visit 3**  **Mail/**  **phone** |
| --- | --- | --- | --- | --- | --- |
|  | D0 | M1-M3  Maximum after intervention | M3 | M6 | M12 |
| Inclusion and exclusion criteria | + |  |  |  |  |
| **Information and consent for the cohort study** | + |  |  |  |  |
| **Randomisation** | + |  |  |  |  |
| **Information and consent to participate in the therapy for patients randomised into the experimental arm** | + |  |  |  |  |
| **Patient contact information** | + |  |  |  |  |
| **Medical examination** | + |  |  |  |  |
| **Back guide and patient diary issued** | + |  |  |  |  |
| ASSESSMENT: | | | | | |
| - Socioprofessional information | + |  |  |  |  |
| - Clinical information regarding lower back pain | + |  | + | + | + |
| - Number of days of sick leave | + |  | + | + | + |
| - Return to work |  |  | + | + | + |
| - Number of periods of sick leave |  |  | + | + | + |
| - Treatments | + |  | + | + | + |
| - Numeric pain scale | + |  | + | + | + |
| - Quebec | + |  | + | + | + |
| - HAD | + |  | + | + | + |
| - MOS SF-12 | + |  | + | + | + |
| - FABQ | + |  |  |  | + |
| - CSQ | + |  |  |  | + |
| - Treatment satisfaction scale |  |  |  |  | + |
| **Adverse Events** |  | + | + | + | + |
| **INTERVENTION: Intensive spa therapy** |  | + |  |  |  |

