## II - 2 - SECONDARY OBJECTIVES

To evaluate the efficacy of a short, intensive and standardised spa therapy intervention on the number of days of sick leave between 6 months and 1 year, as well as pain, function and quality of life at 1 year for patients on sick leave due to lower back pain from 4 to 24 weeks’ duration and for those in which an extended period of sick leave is expected.

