2. With regard to methodology, the limitations of the Zelen method are the risk of contamination through refusal to undergo the intervention (short spa therapy programme). In the Thermarthrose study (Forestier R, ARD 2009), a large-scale, multi-centre trial assessed a specific treatment involving spa therapy vs standard treatment according to a Zelen method, with a 10% rate of contamination. The risk of contamination should be no higher in our study, taking into account:
   1. the lack of risk of the intervention;
   2. the lack of other treatments available;
   3. the duration of the intervention, which will be shorter;
   4. the patients who are on sick leave.

The risk of contamination in the standard-care group is highly unlikely, given that the short spa therapy programme is not currently offered outside this study.

Another risk of the Zelen method is the hypotheses being unblinded for patients. This risk is minimal, as the endpoint assessment visits (at M3, M6 and M12) will be done by post or email (or by phone, if no response is received), which prevents the patients from the two groups from being in contact with each other.

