## VI - 2 - SECONDARY ENDPOINTS

The secondary endpoints will be as follows:

- Area under the curve of pain over the past 48 hours, assessed every fortnight using a numeric scale from 0 to 100 at 1 year;
- Functional assessment at 1 year (Quebec scale);
- Quality of Life assessment at 1 year (MOS SF-12 questionnaire);
- TWIST at 1 year (pain);
- Number of days of sick leave between 6 months and 1 year after enrolment. We have not taken into account the total number of days of sick leave as, by definition, the intervention requires the patients to be available for the duration of the treatment, which will involve sick leave.

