  - Coping strategies: CSQ questionnaire.

Following this visit, the investigator will give the Month 3, 6 and 12 follow-up self-assessment questionnaires which the patient must fill in and return by mail, from the enrolment visit for the control group and from the end of spa therapy for the intervention group.

Patients randomised into the standardised spa therapy arm will receive a start date for the intervention from the secretary at the spa therapy centre, taking into account a maximum time period of 3 months between the enrolment visit and the therapy. The planning of the stay and patient welcome will be arranged by the spa therapy centre, the choice of accommodation will be managed by the French Association for Spa Therapy Research (AFRETH) and transport passes will be managed by the Clinical Research Unit (URC).

Finally, the investigator will provide the patients with the guide on lower back pain, the patient diary containing the self-assessment questionnaires for the various evaluations, as well as the patient card mentioning the patient’s participation in the study.

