## IX -1- 6- Secondary analyses

A linear mixed effects regression model will be used to compare the variations between the groups of the quantitative secondary endpoints (number of days of sick leave, number of periods of sick leave, pain, Quebec scale, MOS SF-12, HAD, FABQ and CSQ). The variable to be studied will therefore be the difference between the randomisation value (D0) and that of interest (1 year), as well as the difference between the randomisation visit and those of the interim visits (3 months and 6 months). The difference in the Δ between the groups will be modelled with the following fixed effects: the group variable (2 modalities), the enrolment value as a quantitative covariate (centred variable), the visit variable (3 modalities) and the interaction between the time and the visit, allowing us to estimate the treatment effect at each visit. The model will therefore allow us to compare the adjusted means (to the baseline value and the values of the interim visits) of the variations between the final visit and the enrolment visit (as well as between the interim visits and the enrolment visit). A random effect on the patient will be added to this model in order to take into account the correlation induced by the repetition of the measurements performed in the same patient. This linear mixed model for repeated measurements (MMRM) allows the assessments performed at each visit to be taken into account, as well as the randomly missing data (the model will also integrate the endpoint values at the different visits, enrolment variables which are potentially predictive of the missing data). The area under the curve of pain between enrolment and 1 year, assessed every week, will be calculated using the trapezoidal rule and compared using the non-parametric Mann–Whitney U test. The Q-TWIST will be calculated from the percentage of time spent by a patient in various states (percentage of time spent in inactivity, time spent with acceptable pain (less than 3 on a scale from 0 to 10 which corresponds to the PASS), time spent with pain greater than 3). The values assigned to these states will be defined at the time of the blind review of the data. The means will be compared using the non-parametric Mann–Whitney U test.

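### IX-1-6 puts sick-leave days and periods, without a window, into a three-visit change-from-D0 model, which does not match the months 6-12 endpoint that VI-2 chose because the spa itself involves leave

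*Protocol*

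**What the plan says.** - **Endpoint.** II-2 names the objective as the "number of days of sick leave between 6 months and 1 year". VI-2 repeats this window, counted from enrolment, and explains why total leave is not used: "by definition, the intervention requires the patients to be available for the duration of the treatment, which will involve sick leave".
- **Analysis.** IX-1-6 opens its list of quantitative secondary endpoints with "number of days of sick leave, number of periods of sick leave" and states no window for either. The modelled variable is the change from D0 to 1 year, "as well as the difference between the randomisation visit and those of the interim visits (3 months and 6 months"). The enrolment value is a covariate, visit has three levels, and the model is described as "allowing us to estimate the treatment effect at each visit".
- **Collection.** The schedule in the General outline marks number of days of sick leave at D0, M3, M6 and M12. It marks "Number of periods of sick leave" at M3, M6 and M12 only. VII-3 asks at each contact for leave since the previous visit, with dates.
- **Spa timing.** VII-1 schedules the stay "taking into account a maximum time period of 3 months between the enrolment visit and the therapy". The schedule collects no sick leave at the intervention visit.

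**The concern.** The endpoint section and the analysis section give different instructions for the same variable. VI-2 judges early leave unsuitable for comparing the arms, because the intervention generates some of it. IX-1-6, followed as written, estimates and tests an arm difference in leave at month 3, where the spa week normally falls. The control arm has no counterpart, since III-4 says the programme is not offered outside the study.

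Two things are at stake. A month 3 sick-leave result could be reported that leans against the spa for the very reason the protocol gave for not looking there. And the prescribed model does not fit either variable: the windowed days endpoint has one value rather than three, and periods have no enrolment value from which to compute a change.

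**Working it through.** **Step 1. Days, both readings.**

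| Reading of IX-1-6 | Consequence |
|---|---|
| Days means the VI-2 endpoint (months 6-12) | No spa-week leave is counted, but there is no M3 or M6 value, so the three-visit model does not apply |
| Days means leave since the previous visit | Three values exist, but the M3 value normally contains the spa week in the spa arm |

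The first reading leaves a model that does not fit its variable. The second conflicts with VI-2.

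**Step 2. Periods.** VI-2 neither lists nor windows them, so there is no window to carry over; only its rationale extends to them. The model needs a D0 value twice, as the subtracted term and as the covariate, and the schedule leaves D0 blank for periods. As written, the model cannot be fitted to periods at any visit.

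**Step 3. Who contributes.** A patient still on leave during the spa week adds no extra leave. A patient who had already resumed work adds about 5 working days and one period.

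**Step 4. Size for days.** The only input from the protocol on return to work is 70% at 1 year in the control group (IV-3). The following are assumptions:
- a constant return rate up to that 70%;
- a stay at month 1, 2 or 3;
- 90% attendance, borrowed from the earlier spa trial that III-4 cites "with a 10% rate of contamination".

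Share back at work at month m: p(m) = 1 − 0.3^(m/12).

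| Spa at month | p(m) | Days per spa patient, p × 0.9 × 5 | At 50% attendance, p × 0.5 × 5 |
|---|---|---|---|
| 1 | 0.0955 | 0.43 | 0.24 |
| 2 | 0.1818 | 0.82 | 0.45 |
| 3 | 0.2599 | 1.17 | 0.65 |

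Expected leave from D0 to M3: with k = −ln(0.3)/12 = 0.1003 per month, (1 − e^(−3k))/k = 2.59 months, or about 79 days. The shift is 0.43/79 = 0.5% to 1.17/79 = 1.5% of that. Counting the spa week as 7 calendar days gives 0.60, 1.15 and 1.64 days, at most 1.64/79 = 2.1%. Dropping the constant-rate assumption and letting 10% to 50% be back at work gives 5 × 0.9 × 0.1 = 0.45 to 5 × 0.9 × 0.5 = 2.25 working days. The upper end is unlikely in patients selected because extended leave is expected.

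With 300 per arm and an assumed SD of 30 days, the standard error is 30 × √(2/300) = 2.45. The shifts in the table at 90% attendance are then 0.43/2.45 = 0.18 to 1.17/2.45 = 0.48 standard errors. A two-sided 5% test with no other effect would reject in about 5% to 8% of trials.

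**Step 5. Size for periods.** The same assumptions give p × 0.9 = 0.09, 0.16 and 0.23 extra periods per spa patient. Whether that is large depends on the SD of the count, on how many working patients would attend, and on when the stay falls. The protocol gives none of these.

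**Step 6. Months 6-12.** A stay within 3 months of enrolment ends well before month 6, so the VI-2 window counted from enrolment contains no spa week.

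**The case against.** **Generic wording.** The interim-visit phrase covers the whole list, including FABQ and CSQ, which after D0 are collected only at M12. A sympathetic reader would carry the VI-2 window over to days. That is fair, and it removes the spa-week problem for days, but the three-visit model still has nothing to work on at M3 and M6.

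**Intention to treat.** Leave taken for the spa is a real consequence of assignment, and counting it by randomised arm is legitimate in a pragmatic trial. This stands. A rejection at M3 for this reason would not be a false positive in the usual sense, and the point is not one of mis-measurement. What remains is that the protocol itself chose not to compare arms on early leave.

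**Detail for the analysis plan.** IX-1 promises a separate plan, and counting windows are often set there. But the protocol already fixes the model, the visits and the variable list. A plan that follows IX-1-6 departs from VI-2, and the reverse.

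**Stronger readings that do not hold.** A reader might infer that VI-2 rules out early periods as well. It speaks only of days. A reader might also infer that the M3 test of periods would very likely come out against the spa. Illustrative calculations for that test run from 7% to 82% rejection, depending on an assumed return curve, SDs of 1.0 or 1.5 and attendance of 50% or 90%. That range is too wide to support a conclusion. The top figure places every stay at month 3, where it may fall after the M3 form.

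Timing is also unsettled. III-4 runs follow-up from enrolment, while VII-1 runs the spa arm's questionnaires from the end of the spa. On the second clock, the spa week would drop out of the M3 value if the stay counted as the previous visit, although no leave is collected then.

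**Conclusion.** The mismatch between IX-1-6 and VI-2/II-2 is real and minor. The days endpoint is defined over months 6-12 and cannot enter a model with M3 and M6 values. A literal M3 contrast reintroduces spa-week leave in one arm. Periods cannot enter a change-from-D0 model because no D0 value is collected.

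For days the shift is negligible, about 0.4 to 1.2 days per spa patient under the constant-rate and 90% attendance assumptions. For periods it could be larger but cannot be quantified from the protocol. Any shift runs against the spa. Return to work at 1 year and sick-leave days in months 6-12 after enrolment are unaffected, and no stated decision rests on the interim sick-leave contrasts.

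**What to change.** In IX-1-6, remove number of days and number of periods of sick leave from the three-visit change-from-D0 model, and add wording such as: *Number of days and number of periods of sick leave are each compared between arms once, as the total over months 6 to 12 after enrolment. Days may be adjusted for the duration of sick leave at D0; periods are analysed without a D0 term. Sick leave at M3 and M6 is described by arm without a test.*

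No new data are needed, because VII-3 already collects leave dates, from which the window after enrolment can be built. The cost is the loss of the M3 and M6 between-arm sick-leave tests. Restricting periods to months 6-12 is a new choice that extends the VI-2 rationale, and should be recorded as such. The change does not settle whether follow-up runs from enrolment or from the end of the spa; that needs its own correction.

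### The secondary mixed model imposes one baseline slope at Months 3, 6 and 12; a baseline-by-visit term would protect the 1-year contrast at almost no cost

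*Protocol*

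**What the plan says.** Protocol IX-1-6 opens: "A linear mixed effects regression model will be used to compare the variations between the groups of the quantitative secondary endpoints". The response is the change from enrolment: "The variable to be studied will therefore be the difference between the randomisation value (D0) and that of interest (1 year"), with the changes to 3 and 6 months analysed alongside it. The fixed effects named are group, "the enrolment value as a quantitative covariate (centred variable), the visit variable (3 modalities"), and one interaction, described as "the interaction between the time and the visit, allowing us to estimate the treatment effect at each visit". Its stated purpose can only be served by a group-by-visit term, so the word for time appears to be a slip for group. Correlation within patients is handled by a random intercept: "A random effect on the patient will be added to this model in order to take into account the correlation". The section then states that the model "allows the assessments performed at each visit to be taken into account, as well as the randomly missing data", and adds that unnamed enrolment variables predictive of missingness will be included. Nowhere does it let the effect of the enrolment value, or of those extra variables, differ by visit.

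The listed endpoint in VI-2 is the 1-year value, for example "Functional assessment at 1 year (Quebec scale").

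**The concern.** Patients enter during an active episode, on sick leave of 4 to 24 weeks, and IV-3 assumes that 70-80% will be back at work at 1 year. A score taken at enrolment may well predict Month 3 better than Month 12. A model with a single slope then adjusts the Month 12 contrast with a slope averaged over three visits. This has two consequences. The adjustment at 1 year is less efficient than it could be. And a likelihood model handles data missing at random only if its mean is right given baseline. With the wrong Month 12 slope, a baseline imbalance between the arms among Month 12 responders is adjusted by the wrong amount.

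**Working it through.** **The plan's own figures.** The protocol gives no figure for this model. The only calculation is for the primary endpoint (IV-3): 70% v 80%, two-sided 5%, 80% power. Per arm, n = (1.960 × √(2 × 0.75 × 0.25) + 0.842 × √(0.7 × 0.3 + 0.8 × 0.2))² / 0.10² = 294, or 588 in total, which agrees with the stated 600. Going from 600 to 700 implies a loss of 1 − 600/700 = 14.3%. These supply only the sample size and the missing fraction used below.

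**Assumptions not in the protocol.** Equal SD at every visit, the baseline correlations shown below, and the strength with which non-response depends on baseline.

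**Precision, by hand.** With complete data, equal SDs and a random intercept, the common slope is the mean of the three visit slopes. The slope of a change score is the correlation minus 1, so only differences between correlations matter. The relative increase in variance at Month 12 is

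(b12 − b_common)² / (1 − r12²).

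| Correlations M3/M6/M12 | Mean | Gap at M12 | By hand | Simulated |
|---|---|---|---|---|
| 0.4/0.4/0.4 | 0.400 | 0 | 0% | 0% |
| 0.7/0.6/0.5 | 0.600 | −0.100 | 0.0100/0.75 = 1.3% | about 0-1% |
| 0.5/0.4/0.25 | 0.383 | −0.133 | 0.0178/0.9375 = 1.9% | 1.6% |
| 0.7/0.5/0.3 | 0.500 | −0.200 | 0.0400/0.91 = 4.4% | 3-5% |
| 0.6/0.45/0.2 | 0.417 | −0.217 | 0.0469/0.96 = 4.9% | 6% |

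The simulations used 350 per arm and the random-intercept model, with 2,500 to 3,000 trials per case.

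**Bias, by hand.** Under no treatment effect, the bias is roughly (b12 − b_common) × D, where D is the between-arm difference in mean baseline, in SD, among Month 12 responders. The scenarios below have 14% missing at Month 12, with non-response depending on baseline in opposite directions in the two arms.

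| Correlations | Log-odds per baseline SD | D | By hand | Simulated, common slope | Simulated, slope by visit |
|---|---|---|---|---|---|
| 0.6/0.6/0.6 | 0.5 | −0.14 | 0 | 0.002 | 0.002 |
| 0.6/0.6/0.6 | 1.0 | −0.25 | 0 | −0.001 | −0.001 |
| 0.7/0.6/0.5 | 0.5 | −0.14 | 0.014 | 0.016 | −0.002 |
| 0.7/0.6/0.5 | 1.0 | −0.25 | 0.025 | 0.031 | −0.001 |
| 0.7/0.5/0.3 | 0.5 | −0.14 | 0.028 | 0.038 | 0.002 |
| 0.7/0.5/0.3 | 1.0 | −0.25 | 0.050 | 0.064 | 0.001 |

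The Monte Carlo error of each simulated bias is about 0.078/√2500 = 0.0016 SD or less. The hand formula runs a little low because the common slope equals the simple mean only with complete data. A separate simulation with SD 20 and log-odds 0.5 gave 0.51 points (0.51/20 = 0.026 SD) for 0.5/0.4/0.25 and 0.91 points (0.91/20 = 0.046 SD) for 0.6/0.45/0.2.

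**When the bias vanishes or shrinks.** If non-response depends on baseline in the same direction and strength in both arms, D is about 0 and the simulated bias is at most 0.003 SD. With about 20% missing, correlations 0.7/0.5/0.3 and log-odds 1.0, dependence in one arm only gave 0.044 SD, against 0.088 SD for opposite directions.

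**Test size.** In the opposite-direction scenarios, type I error with a common slope was 7.7-10.0% (0.7/0.6/0.5) and 11.6-19.2% (0.7/0.5/0.3). With visit-specific slopes it was 6.8-7.2% and 8.1-8.4%.

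**Sensitivity.** Section IX-1-6 also calls the model an MMRM. With an unstructured covariance, correlations 0.7/0.5/0.3 gave a variance increase of about 10-17% in a smaller run (600 trials, up to about 20% missing).

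**The case against.** The strongest reply is that covariate-by-visit terms are usually settled in a statistical analysis plan, that randomisation already protects the contrast when data are complete, and that the bias needs three things together: a slope that decays, Month 12 non-response related to baseline, and a relation that differs by arm. None of these is documented. The design also works against the third. Section III-4 adopts the modified Zelen method so that controls are less likely to withdraw or behave differently, and adds reminders, help with questionnaires and a voucher.

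Much of this stands, and it keeps the point minor. It does not remove it. The protocol itself names the model terms, so the common slope is a stated choice. The Zelen design limits differential response but cannot exclude it: only the intervention arm gives a second consent, and its questionnaires run from the end of spa therapy while those of controls run from enrolment (VII-1).

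Stronger readings that a reader might infer, and that the protocol does not support:

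- *The missing-data claim fails outright.* It is weakened only when both conditions hold, and then by a few hundredths of an SD.
- *Precision is always lost.* With equal slopes there is no loss.
- *The list of fixed effects is complete.* The same section adds unnamed enrolment variables. That clause does not help here, because it lets no baseline effect vary by visit.
- *Every secondary endpoint is affected.* The pain AUC and TWIST are compared by Mann-Whitney test, and FABQ and CSQ have a single follow-up, at Month 12.
- *The excess type I error is all due to the missing term.* What remains after the fix (6.8-8.4%) is partly due to the random-intercept, equal-variance structure.

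**Conclusion.** The point holds as a minor, conditional weakness in a stated model. Under the random-intercept model as written, the variance of the 1-year contrast is 0-6% higher than necessary, depending on how far the baseline association decays. Bias of about 0.02-0.06 SD arises only when slope decay is combined with baseline-dependent non-response that differs by arm, here taken in opposite directions with 14% missing. It is about zero otherwise. All correlations and missingness strengths are assumptions. Of the endpoints listed in VI-2, the point reaches Quebec and SF-12; it also reaches the HAD and pain scores that IX-1-6 puts in the model. The primary comparison, a chi-squared test, and its sample size are untouched.

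**What to change.** In IX-1-6, add the interaction between the centred enrolment value and visit to the fixed effects, so that each visit has its own baseline slope. In the same sentence, correct the interaction now written as time by visit to group by visit. Report the Month 12 group difference from that model. The cost is two degrees of freedom and an edit before the database is frozen. No new data are needed, because the enrolment value is already collected and already in the model. In the equal-slope cases the extra term cost no measurable precision.

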## VII - 3 - FOLLOW-UP VISITS after the intervention

Patients will undergo follow-up at Months 3, 6 and 12. Follow-up will be done by post or email, depending on the patient’s preference, together with a telephone call if no response is received.

The following data will be evaluated:

- Professional status and return to work;
- Periods of sick leave since the previous visit (dates and number of days of sick leave);
- Assessment of pain over the past 48 hours, assessed using a numeric scale from 0 to 100;
- Lower back pain progress;
- Treatment since the previous visit;
- Adverse events collected;
- Functional indices: Quebec scale;
- Anxiety/Depression: HAD questionnaire;
- Quality of Life: MOS SF-12 questionnaire;
- Fear-avoidance beliefs: FABQ questionnaire (only at the Month 12 assessment);
- Coping strategies: CSQ questionnaire (only at the Month 12 assessment);
- Treatment satisfaction (only at the Month 12 assessment).

Pain over the past 48 hours will also be systematically evaluated once every fortnight by phone (using a numeric scale from 0 to 100). VOICE RESPONSE SYSTEM

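### The mixed model for the secondary endpoints names a redundant time by visit interaction and omits group by visit, so as written it gives one averaged treatment effect, not the 1-year effect

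*Protocol*

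**What the plan says.** Protocol section IX-1-6 defines one linear mixed model for the quantitative secondary variables: days and periods of sick leave, pain, Quebec, SF-12, HAD, FABQ and CSQ. The response is the change from D0 at 1 year, and also at 3 and 6 months. The fixed effects are:

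- treatment arm, with two levels
- the D0 measurement, centred, as the only covariate
- two further terms, given as "the visit variable (3 modalities) and the interaction between the time and the visit, allowing us to estimate the treatment effect at each visit"

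A patient random effect is added. On what is then compared, the section's words are "compare the adjusted means (to the baseline value and the values of the interim visits) of the variations between the final visit and the enrolment" (the sentence goes on to say the same of M3 and M6). Later it adds that "the model will also integrate the endpoint values at the different visits, enrolment variables which are potentially predictive of the missing data".

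Section VI-2 sets the secondary endpoints at 1 year, for example "Functional assessment at 1 year (Quebec scale"), and section II-2 states the objectives at the same time point. Section VII-3 collects "Fear-avoidance beliefs: FABQ questionnaire (only at the Month 12 assessment") and restricts the CSQ in the same way. The summary and the visit schedule agree: after D0, both are measured once.

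**The concern.** The only route by which this model could give a treatment effect at each visit is a term that lets the group difference vary by visit. The term that is named does not do that. An analyst who programmed the list as it stands would report a single group coefficient pooled over 3, 6 and 12 months against endpoints defined at 1 year. If the effect of a five-day programme fades, a 1-year benefit could be reported that is no longer there. If it builds up, a real 1-year benefit would be diluted.

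For sick-leave days there is a further twist. VI-2 deliberately confines the endpoint to the second half-year, because attending the programme itself involves sick leave. If each questionnaire covers the interval since the previous contact, as VII-3 describes, pooling over visits brings the earlier intervals back in.

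Two smaller points in the same paragraph need attention. The parenthesis on what the means are adjusted for can be read as conditioning on outcomes measured after randomisation. And FABQ and CSQ are assigned to a three-visit model although they have one follow-up measurement.

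**Working it through.** The protocol gives no numerical figure for this model. The 300 per arm in IV-3 belongs to the primary endpoint. The usual formula for 70% against 80% gives 294 per arm, so that figure reproduces, but it does not bear on this point.

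**1. What the listed terms can estimate.** Count the independent columns of the fixed-effects design:

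- intercept 1 + group 1 + baseline 1 + visit (3 levels) 2 = 5
- adding time by visit: still 5. Each visit has one time value (3, 6 or 12 months), so every product of time and a visit indicator is a multiple of that indicator. Treating time as a factor changes nothing.
- adding group by visit instead: 5 + 2 = 7

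A numerical rank check gave the same 5, 5 and 7. Only the last design has a separate group difference at each visit.

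**2. What the single group coefficient is.** Write d3, d6 and d12 for the group differences at the three visits. With complete data:

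common effect = (d3 + d6 + d12) / 3

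gap from the 1-year effect = (d3 + d6 + d12) / 3 − d12 = (2/3) × [(d3 + d6)/2 − d12]

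The gap is zero if the effect is constant, or if the M3 and M6 effects happen to average to the M12 effect.

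**3. Size under assumed effects.** The protocol gives no expected effects by visit, so these are assumptions. The simulation used 300 per arm, complete data at three visits, patient and residual SDs of 1, and 500 replicates.

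| Assumed d3 / d6 / d12 | Formula: common effect | Simulated, terms as listed | Simulated M12 contrast with group by visit | True M12 effect |
|---|---|---|---|---|
| 0.5 / 0.5 / 0.5 | 0.500 | 0.491 | 0.493 | 0.5 |
| 0 / 0 / 0.5 | 0.167 | 0.165 | 0.498 | 0.5 |
| 0.5 / 0.25 / 0 | 0.250 | 0.243 | −0.005 | 0 |
| 0.6 / 0.45 / 0.3 | 0.450 | 0.456 | 0.308 | 0.3 |

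The simulated common effect is within 0.009 of the formula in every row. Replacing the interaction recovers the 1-year effect in every row.

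**4. FABQ and CSQ.** With one post-baseline value per patient, the visit factor has one level and the patient random effect cannot be separated from the residual. What remains is the M12 change regressed on group and baseline, which is an ANCOVA. The group coefficient is the same whether the response is the M12 value or the change.

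**The case against.** The strongest reply is that this is a slip of one word. The sentence states its purpose, and the next sentence promises adjusted comparisons at the final and at the interim visits. Only group by visit delivers either, and VI-2 fixes the time point independently. Section IX-1 provides for a statistical analysis plan before database freeze, where the code would be settled. With a constant effect, the literal model gives the right answer anyway.

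Most of this stands. A reader might infer that the trial cannot estimate its 1-year secondary effects. The documents do not support that, because the stated aim shows what was meant. What does not fall away is the text itself: the protocol does not leave the model to a later document but lists its terms, and lists them wrongly. A later plan that follows the list inherits the error; one that departs from it silently invites the question of when the model was chosen.

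Three stronger readings are tempting and should not be drawn:

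- **Interim values as covariates.** A reader might take "compare the adjusted means (to the baseline value and the values of the interim visits") to mean that the 1-year effect is estimated net of M3 and M6. With slope b on the M6 value that would give d12 − b × d6, so an assumed slope of 0.5 and a constant effect would halve it. But the enrolment value is the only covariate listed, and the M3 and M6 changes are defined as responses in the same model. The phrase is more likely a loose account of how repeated outcomes are used. It needs rewording; the halving is not a consequence of the plan.
- **The MMRM label.** The text names a patient random effect but no residual structure. That detail can be left to the analysis plan and does not change which treatment effect is targeted.
- **Missing baseline by visit or site terms.** These are preferences and are not needed to repair the interaction.

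FABQ and CSQ are not among the endpoints in VI-2, so that contradiction touches no named secondary endpoint.

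**Conclusion.** The point holds as a misstated analysis rule. As listed, the fixed effects yield one treatment effect averaged over three visits, while the same sentence claims an effect at each visit and the objectives ask for 1 year. The discrepancy is two-thirds of the difference between the mean interim effect and the 1-year effect. It is nil if the effect is constant, and in the assumed scenarios as large as 0.25 against a true 0, or 0.17 against a true 0.5. These figures assume complete data and illustrative effects; with dropout the visit weights would shift.

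The scope is limited to the quantitative secondary variables analysed with this model, which include three endpoints of VI-2: Quebec, SF-12 and sick-leave days. The chi-squared test of the primary endpoint and the Mann–Whitney comparisons of pain AUC and TWIST do not depend on it. The intended term is very probably group by visit, so this is a correction that should be made, not a threat to the trial's main conclusion.

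**What to change.** In section IX-1-6:

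1. Replace the time by visit interaction with group by visit, and name the M12 group contrast from this model as the estimate for the 1-year secondary endpoints.
2. Reword the parenthesis on adjusted means, and the later sentence on integrating endpoint values, to say that M3 and M6 values enter only as repeated responses and never as covariates. Where the interim effects run in the same direction as the 1-year effect, conditioning on them would remove part of it.
3. Take FABQ and CSQ out of the three-visit model and analyse each by ANCOVA of the M12 value (or change) on group and baseline.

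The cost is the wording of one paragraph and standard SAS code. Data collection, visits and sample size do not change. It should be done before the database is frozen and the data unblinded, so that the choice of model cannot be questioned afterwards.
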